#### **Secondary Objectives**

- Evaluate diagnostic accuracy of lentigo maligna with different clinical-instrumental algorithms.
- Define which RCM features distinguish lentigo maligna from benign facial macules, such as solar lentigo, freckles, actinic keratoses and seborrheic keratoses, and to develop an easy-to-use diagnostic algorithm.
- Evaluate the accuracy of basal cell carcinoma diagnosis with RCM.
- Analyze and compare the difference of costs of diagnosis with RCM compared to standard histological examination.
- Compare the time required to perform RCM compared to standard histological examination.

Hypothesis to be tested: the advantage of the integration of RCM to the current clinical-diagnostic pathway (clinical-dermoscopic). Outcomes will be measured in terms of the early diagnosis (number of unnecessary excisions), diagnostic safety (number of melanomas diagnosed), and cost-benefit / efficacy calculation based on the drug model. economic developed within the studio.

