b) "Clinical and dermoscopic evaluation only": following routine therapeutic care (clinical-dermoscopic examinations) clinicians of patients with suspicious lesions (at least one major or minor clinical and / or dermoscopic criterion for malignancy, as per inclusion / exclusion criteria), will make a clinical decision (removal or digital dermoscopic follow-up) without RCM evaluation.

Each participating center will be responsible for its own case history and clinical decisions. Each center will take care of the collection and storage of data. At interim analysis (18 months) collected data and preliminary results will be evaluated collectively and discussed. The investigators at the participating centers have high-level therapeutic-diagnostic pathways in place, as documented by the numerous publications produced by these centers, however, in case of significant discrepancies among the interim clinical performance data, or if requested by individual investigators, some cases may be evaluated independently by other investigators in order to verify diagnostic agreement. These cases may derive either from direct indications from the investigators or randomly selected from the collected cases.

Images will be anonymized and only essential clinical data (sex / age, any significant present or past pathologies) will be provided to the other evaluators.

The definition of the head / neck lesion subset is as follows:

1. Malignant macules with histological diagnosis of melanoma;
2. Benign macules with histological diagnosis of actinic keratoses, solar lentigos, lichen planus-like keratosis, seborrheic keratoses, freckles and junctional / compound / dermal nevi;
3. Benign macules not subjected to biopsy and with clear and defined parameters of clinical, dermoscopic and confocal microscopy benignity;

The main outcome will be the rate of malignant lesions identified within the "RCM evaluation + clinical and dermoscopy evaluation" compared to "Clinical and dermoscopic evaluation only" study arms.

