Sensitivity, specificity, diagnostic accuracy, odds ratios (OR) with the 95% confidence interval will be evaluated. Several algorithms will be developed for the diagnosis of lentigo maligna in consecutive head / neck injuries. In particular, the positive and negative predictive values for each individual parameter analyzed will be measured and the combination of parameters capable of increasing diagnostic accuracy and reducing the number of unnecessary excisions, will be identified.

RCM features will be systematically analyzed to distinguish lentigo maligna from benign facial lentigos.

The time required for the assessment of face / neck injuries will be calculated and compared within the two groups.

The subgroup of non-melanocytic malignant lesions should include consecutive cases defined as:

1. Carcinomatous neoformations with histological diagnosis of basal cell carcinoma
2. Carcinomatous neoformations with histological diagnosis of squamous cell carcinoma
3. Benign neoformations with histological diagnosis of actinic keratoses, solar lentigos, lichen planus-like keratosis, seborrheic keratoses, ephelides and junctional / compound / dermal nevi.
4. Benign neoformations not subjected to histological analysis and with clear and defined parameters of clinical, dermoscopic and RCM benignity.

The main result is to evaluate the rate of histologically confirmed, excised basal cell carcinomas detected in the "RCM evaluation + clinical and dermoscopy evaluation" compared to "Clinical and dermoscopic evaluation only" study arms.

Sensitivity, specificity, diagnostic accuracy, odds ratios (OR) with the 95% confidence interval will be evaluated. Finally, the differences between the time, technical and human resources required within the "RCM evaluation + clinical and dermoscopy evaluation" compared to "Clinical and dermoscopic evaluation only" study arms.

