### **Statistical analysis**

Randomization: the "sample" function of STATA 13 (STATA Corp. College Station, Texas 2014) will be used weekly to predetermine the allocation of the subjects, in an alternating random manner, into the two study arms.

In the Coordinating Center, an estimated 800 patients will be enrolled (a total of 400 cases per study arm).

Outcomes include diagnostic safety of the RCM tool (measured by the number of excisions in relation to the number of melanomas diagnosed), a cost-benefit / efficacy calculation (based on an economic-drug model developed within the studio).

The estimated number of delayed cancer diagnosis within the "RCM evaluation + clinical and dermoscopy evaluation" study group is less than 1%.

Study power calculation: The expected percentage of melanomas identified in the "Clinical and dermoscopic evaluation only" group is 7.3% (Carli P, De Giorgi V, Nardini P, Seidenari S, Pellacani G, Peris K, Piccolo D, Rubegni P, Perotti R. *Skin Cancer Day in Italy: tumor detection rate and pattern of referral of open access clinics in an intermediate melanoma risk population. Eur J Dermatol* 2003; 13: 76-79) and for the "RCM evaluation + clinical and dermoscopy evaluation" group is 14% (Guitera P, Pellacani G, Longo C, Seidenari S,

As outlined in literature, approximately 22.4% of patients with "atypical" lesions are sent for treatment in highly experienced centers, equipped with digital dermoscopy (Alarcon I, Carrera C, Palou J, Alos L, Malveyh J, Puig S. *Impact of in vivo reflectance confocal microscopy on the number needed to treat melanoma in doubtful lesions. Br J Dermatol.* 2014; 170: 802-8) therefore, the enrolment of at least 2375 patients is required. Each collaborating center will enroll about 800 subjects.

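### Lentigo maligna algorithms are chosen for their accuracy in the only head/neck lesion set defined; accuracy taken from that set would be optimistic, and no correction is stated

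*Protocol*

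**What the plan says.** In the Protocol, Secondary Objectives has two relevant items. One is to "Evaluate diagnostic accuracy of lentigo maligna with different clinical-instrumental algorithms". The other is to find the RCM features that separate lentigo maligna from benign facial macules and "to develop an easy-to-use diagnostic algorithm".

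Design and description of the study gives the method. A single lesion set is introduced with "The definition of the head / neck lesion subset is as follows", followed by three categories: malignant with histology, benign with histology, and benign without biopsy. The section then says "Several algorithms will be developed for the diagnosis of lentigo maligna in consecutive head / neck injuries". It adds that "the positive and negative predictive values for each individual parameter analyzed will be measured" and that "the combination of parameters capable of increasing diagnostic accuracy and reducing the number of unnecessary excisions, will be identified".

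Just before the algorithm sentences, after the outcome that compares the two arms, stands a general sentence on accuracy measures: "Sensitivity, specificity, diagnostic accuracy, odds ratios (OR) with the 95% confidence interval will be evaluated". It names neither the lesions nor the rule it applies to.

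The protocol mentions no training and test split, resampling or external lesion set for these algorithms. The testing and adapting described under Statistical analysis concerns the cost-utility model.

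**The concern.** The stated criterion for choosing a combination is the accuracy it gives. When many candidate parameters are screened and the best combination is kept, part of its apparent performance is chance fit to those particular lesions. Scored on the same lesions, its sensitivity and specificity come out too high on average. A standard 95% interval around them treats the rule as fixed in advance, so it is centred too high and ignores the uncertainty of the selection. Developing several algorithms adds a further choice of the same kind.

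The algorithm is meant to be easy to use on facial macules. The background section warns that an unrecognised lentigo maligna, wrongly treated, may progress. An overstated sensitivity would understate how many lentigo maligna lesions the rule misses.

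**Working it through.** **1. What the text fixes.** Three elements stand in the protocol: selection by accuracy, evaluation of algorithm accuracy as an objective, and one head/neck subset. One element is missing: the lesions on which the selected combination is to be scored. With one subset and no resampling described, the natural default is to score it on the development lesions.

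**2. Is there a plan figure to reproduce?** No. The protocol gives no number of head/neck lesions, no number of candidate parameters and no target accuracy for the algorithms. The figure in "the calculated number of subjects is 532" sizes the comparison of melanoma rates between arms and is not an input here.

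**3. Rough count of malignant lesions (orientation only).** Statistical analysis expects 14% melanomas in the RCM arm. RCM features come mainly from that arm.

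- With 532 subjects: 532 / 2 × 0.14 = 266 × 0.14 ≈ 37 melanomas at all sites.
- If 14% applied to all 2375 enrolled: 2375 / 2 × 0.14 ≈ 166.
- Assumed head/neck share 10% to 30% (not in the protocol): about 4 to 11 on the first basis, about 17 to 50 on the second.

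Lentigo maligna work at the collaborating centres could add lesions, so these are not bounds.

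**4. Simulation on the sensitivity + specificity scale.** Assumed: 20 binary features; the best 4 chosen by univariable z; logistic score; Youden cut-off; 300 runs, each scored on the development lesions and on 8,000 new ones. Informative features have prevalence 50% in malignant and 20% in benign lesions; the others have 30% in both. Optimism = (apparent sensitivity + specificity) − (true sensitivity + specificity).

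| Malignant / benign | 4 informative features | None informative |
|---|---|---|
| 15 / 85 | 0.244 | 0.435 |
| 30 / 170 | 0.113 | 0.303 |
| 60 / 340 | 0.046 | 0.220 |
| 120 / 680 | 0.012 | 0.155 |

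For 15 / 85 with 4 informative features: (0.800 + 0.789) − (0.586 + 0.759) = 0.244. Most of this is sensitivity, 0.80 apparent against 0.59 true. At 120 / 680, sensitivity is 0.71 against 0.70.

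**5. Simulation on the AUC scale.** Assumed: 30% lentigo maligna; 15 to 25 binary features; the 5 with the largest prevalence difference summed into a score; Youden cut-off; 400 runs, each tested on 4,000 new lesions. Informative features have prevalence 0.50 against 0.30.

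- 100 lesions, none informative: apparent 0.69 to 0.72, true 0.50, gap 0.19 to 0.22.
- 300 lesions, none informative: apparent 0.61 to 0.63, true 0.50, gap 0.11 to 0.13.
- 100 lesions, two informative: apparent 0.73 to 0.75, true 0.57 to 0.58, gap about 0.15 to 0.18; sensitivity 0.67 to 0.71 apparent, 0.50 to 0.51 true.
- Five informative: gap about 0.02 with 300 lesions and about zero with 800.

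**6. Reading.** Both simulations agree on the direction. The size depends on the number of malignant lesions and the strength of the features. The rough counts in step 3 fall well short of 120 malignant lesions, mostly where the simulated optimism is not negligible, but they rest on an assumed head/neck share.

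**The case against.** The strongest reply is that the protocol never says the selected rule will be scored on its own development lesions. The sentence on sensitivity and specificity comes before the algorithm sentences and follows the arm-comparison outcome. The same sentence recurs for the non-melanocytic subgroup, where no algorithm is developed, so it reads as a stock statement. The first secondary objective could also mean comparing diagnostic pathways (clinical, dermoscopic, RCM) and not data-selected rules. Internal validation of a secondary objective is often left to a SAP. Screening parameters and choosing a combination is simply what algorithm development is.

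Much of this stands. A reader might infer that the protocol prescribes same-lesion scoring with naive intervals and that the reported accuracy is therefore certain to be materially too high. The text does not support that: the scoring lesions are unstated, and the bias can be negligible. The case with no informative feature is an extreme, since the protocol reports earlier successful use of RCM on flat facial lesions. A reader might also link the guidelines promised in the Conclusion to this algorithm, but that sentence concerns integrating RCM into diagnosis.

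One part does not answer the point. The protocol itself fixes the selection criterion, the objective of evaluating accuracy and the single subset. Whether separate validation lesions exist is a matter of design, and none are described.

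**Conclusion.** The point holds in conditional form. The protocol selects a combination by its accuracy, makes algorithm accuracy an objective and provides one lesion set. If the accuracy of the selected combination is taken from that set, it is biased upward, and its ordinary 95% interval ignores the selection.

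The size is not determined by the documents. On assumed inputs it runs from about 0.01 to 0.44 in sensitivity + specificity, and from about zero to about 0.2 in AUC. It is small with several hundred lesions and informative features, and large with around 100 lesions and few or no informative ones. A claim of a particular inflation in this trial would go beyond the text.

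This concerns a secondary objective. The randomised comparison, the number needed to excise and the cost-utility model are unaffected.

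**What to change.** In Design and description of the study, after the sentence on identifying the combination, state that the accuracy of any data-selected algorithm will be reported with optimism correction. Use a bootstrap, or cross-validation, that repeats the whole process in each resample: parameter screening, choice of combination and choice of cut-off. Resample by patient, because Data collection allows several lesions per patient. Show uncorrected figures only beside the corrected ones, labelled as apparent. Leaving out one centre at a time is a possible supplement, but it may be unstable if malignant head/neck lesions are few or unevenly spread over the three centres.

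The cost is slightly more analysis work and no new data. The downside for the sponsor is that the reported accuracy will be lower.

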### **Statistical analysis**

Randomization: the "sample" function of STATA 13 (STATA Corp. College Station, Texas 2014) will be used weekly to predetermine the allocation of the subjects, in an alternating random manner, into the two study arms.

In the Coordinating Center, an estimated 800 patients will be enrolled (a total of 400 cases per study arm).

Outcomes include diagnostic safety of the RCM tool (measured by the number of excisions in relation to the number of melanomas diagnosed), a cost-benefit / efficacy calculation (based on an economic-drug model developed within the studio).

The estimated number of delayed cancer diagnosis within the "RCM evaluation + clinical and dermoscopy evaluation" study group is less than 1%.

Study power calculation: The expected percentage of melanomas identified in the "Clinical and dermoscopic evaluation only" group is 7.3% (Carli P, De Giorgi V, Nardini P, Seidenari S, Pellacani G, Peris K, Piccolo D, Rubegni P, Perotti R. *Skin Cancer Day in Italy: tumor detection rate and pattern of referral of open access clinics in an intermediate melanoma risk population. Eur J Dermatol* 2003; 13: 76-79) and for the "RCM evaluation + clinical and dermoscopy evaluation" group is 14% (Guitera P, Pellacani G, Longo C, Seidenari S,

As outlined in literature, approximately 22.4% of patients with "atypical" lesions are sent for treatment in highly experienced centers, equipped with digital dermoscopy (Alarcon I, Carrera C, Palou J, Alos L, Malveyh J, Puig S. *Impact of in vivo reflectance confocal microscopy on the number needed to treat melanoma in doubtful lesions. Br J Dermatol.* 2014; 170: 802-8) therefore, the enrolment of at least 2375 patients is required. Each collaborating center will enroll about 800 subjects.

The differences in the frequency of diagnoses obtained in the two study groups will be calculated and compared using the X2 test (chi-square). As a measure of diagnostic efficiency, the NNE (Number Needed to Excise), corresponding to the ratio between malignant lesions and excised benign lesions, obtained in the two different arms, will be calculated. Kolmogorov-Smirnov two-sample Z-test will be used to compare the differences in NNE obtained in the 2 arms. The cost - utility model will be developed in collaboration with the University of Pavia, Department of Pharmacological Sciences, in order to quantify the economic impact on the National Health System.

The model will take into account the costs of treatment (surgery / drug), examination, follow-up visits, devices and histopathology evaluation. The model will be constructed considering two possible alternatives: surgical excision versus RCM examination of equivocal lesions. The model will be tested and adapted based on the real data obtained from the prospective study.

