### **Scope of the Project**

#### **Principal Objective**

- Evaluate cost-benefit deriving from the presumed reduced number of unnecessary excisions given the accuracy of diagnosis with RCM.
- develop and test a regional triage system for skin cancers based on a radial hospital network model with the systematic integration of RCM into current clinical practice.
- Evaluate diagnostic sensitivity and specificity in screening patients at high risk of skin cancer with the use of the manual RCM tool.

Experimental design 1 aims at a reduction of over 30% of unnecessary excisions, with less than 2% of melanoma delayed

diagnosis (compared with dermoscopy delayed melanoma diagnosis ranging from 7.6 to 16.2%, for digital monitoring (10)),

and with no tumors thicker than 0.5 mm delayed.

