### **Design and description of the study**

This is a prospective randomized 2-arm study (performed in 3 hospitals). Consecutive patients with at least 1 lesion suspicious of melanoma (following clinical and dermoscopy evaluation) will be enrolled. Patients will be randomized to the standard therapeutical care ("Clinical and dermoscopy evaluation only") or standard therapeutical care + RCM integration ("RCM evaluation + clinical and dermoscopy evaluation") following identification of a suspicious lesion during the standard therapeutical care.

The main objective is to evaluate the safety of the integration of RCM (diagnostic identification of melanomas) and cost-effectiveness in terms of the comparison of the number of excisions needed to identify 1 melanoma (including the follow-up period). A cost-utility model will be developed to quantify the impact of the proposed triage system on health care costs and diagnostic effectiveness. This model will be tested on the study population.

Patients will be selected consecutively among patients with suspected skin cancer.

Randomization will be allocated at a 1:1 ratio and patients will be allocated to the “RCM evaluation + clinical and dermoscopy evaluation” or “Clinical and dermoscopic evaluation only” following standard therapeutic care; patients allocated to “Clinical and dermoscopic evaluation only” will likely require immediate biopsy for diagnosis, whereas clinicians of patients allocated to the “RCM evaluation + clinical and dermoscopy evaluation” can decide based on RCM evaluation whether to excise the lesion or refer the patient to subsequent digital follow up. Lesions referred to follow-up will be monitored for at least 6 months, and excised if significant changes are observed on dermoscopy.

In detail, the therapeutic-diagnostic pathway for each study arm are as follows:

a) "RCM evaluation + clinical and dermoscopy evaluation": following routine therapeutic care (clinical-dermoscopic examinations) clinicians of patients with suspicious lesions (at least one major or minor clinical and / or dermoscopic criterion for malignancy, as per inclusion / exclusion criteria) will be able to evaluate the lesions with RCM. A clinical decision (removal or digital dermoscopic follow-up) will be made based on the RCM evaluation.

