#### **Expected results, possible problems and solutions**

The project aims to prove the reduction of more than 30% of unnecessary excisions, with <2% of melanomas with delayed diagnosis (compared with the delayed melanoma diagnosis associated with dermoscopy, which has an estimated range of 7.6- 16.2%. [*Salerni G et al JEADV 2012*), and no thin tumor (thickness > 0.5mm) diagnosed late. The integration of the RCM tool into the standard care pathway is estimated to demonstrate a possible saving of ~€ 30,000 /100,000 inhabitants / year. The risk of misdiagnosing a true melanoma with RCM is minimized, as patients with clinical/dermoscopically suspicious lesions are referred to digital dermoscopy follow-up, where any changes should be recognized within a short interval of time, without risk to the patient's health. The risk of patient loss to follow-up will be minimized, by the allocation of a follow-up appointment during the initial consultancy visit, with the activation of a dedicated telephone number for enrolled patients who may need to modify their pre-programmed follow-up. Additionally, patients who do not present for the pre-programmed consultancy visit will be contacted by telephone.

The cost-utility model, adaptable to different local situations, will be published and made available for the implementation of similar triage systems according to a radial model for the management of skin neoplasms.

The integration of RCM in the triage of high-risk patients will demonstrate the real advantages, by calculating RCM diagnosed melanomas which may have been misdiagnosed with video microscopy alone, due to the lack of significant dermoscopic features.

The risk of increasing the number of unnecessary excisions will be considered and verified periodically through an interim analysis every 6 months.

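### Diagnostic safety is defined as excisions per melanoma, which can improve while melanomas are missed and ignores delay; the planned size gives almost no support for proving under 2% delayed.

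*Protocol*

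**What the plan says.** The protocol describes safety in three places, and not in the same way.

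- *Statistical analysis*: "Outcomes include diagnostic safety of the RCM tool (measured by the number of excisions in relation to the number of melanomas diagnosed". The same section later introduces "the NNE (Number Needed to Excise), corresponding to the ratio between malignant lesions and excised benign lesions" and calls it a measure of diagnostic efficiency.
- *Secondary Objectives*, in the hypothesis paragraph: "diagnostic safety (number of melanomas diagnosed".
- *Design and description of the study*: safety is the identification of melanomas, while cost-effectiveness is judged by "the number of excisions needed to identify 1 melanoma (including the follow-up period".

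Delayed diagnosis also appears in three places.

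- *Principal Objective* sets an aim: "with less than 2% of melanoma delayed".
- *Expected results, possible problems and solutions* repeats it as something the project aims to prove: "with <2% of melanomas with delayed diagnosis".
- *Statistical analysis* gives an expectation of less than 1% for the RCM group, beginning "The estimated number of delayed cancer diagnosis within the". It speaks of cancer rather than melanoma and does not say what the percentage is taken of.

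The only sample-size calculation concerns melanomas identified, 7.3% against 14%.

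**The concern.** In the RCM arm the clinician may send a suspicious lesion to digital follow-up instead of excising it. The harm that a safety outcome has to detect is therefore a melanoma diagnosed late or not at all. Excisions per melanoma mixes that harm with the benefit under study, fewer benign excisions, so a large enough benefit can hide the harm. A reader who takes the statistics section at its word would report an efficiency gain as evidence of safety.

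The delayed-melanoma figure does address the harm, but it has no sample-size basis. If few melanomas are expected, a count of zero or one delayed case is compatible with a true rate well above 2%.

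**Working it through.** **The plan's own size.** Inputs from *Statistical analysis*: 7.3% and 14%, power 80%, alpha 0.05, total 532. With a one-sided alpha, the pooled two-proportion formula gives

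n = [1.645 × √(2 × 0.1065 × 0.8935) + 0.842 × √(0.073 × 0.927 + 0.14 × 0.86)]² / 0.067² ≈ 262 per arm,

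or 524 in total, within 3% of 532. A two-sided alpha gives 664. The protocol does not state which was used. Then 532 / 0.224 = 2375. This yields 266 or about 1188 patients per arm, depending on whether all those enrolled contribute. None of it concerns delayed melanomas.

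**How the ratio behaves.** Let M melanomas and B benign lesions be excised, so that excisions per melanoma = (M + B)/M = 1 + B/M. If a share b of benign lesions is spared and a share m of melanomas is missed, it becomes 1 + (1 − b)B / [(1 − m)M]. It falls exactly when b > m.

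Illustration with 1000 lesions, of which 73 are melanomas (7.3%) and 927 benign:

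| Situation | Excisions / melanomas | Ratio |
|---|---|---|
| All excised | 1000 / 73 | 13.7 |
| 10 melanomas missed, no benign lesion spared | 990 / 63 | 15.7 |
| 30% of benign spared, none missed | 722 / 73 | 9.9 |
| 30% of benign spared, 10 missed | 712 / 63 | 11.3 |
| 30% of benign spared, 20 missed (27%) | 702 / 53 | 13.2 |

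The 30% is the protocol's own target for unnecessary excisions. NNE as the protocol words it is malignant over benign, M/B, so it runs in the opposite direction but depends on the same quantity.

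**Delay.** A melanoma excised in follow-up adds one excision and one melanoma, exactly as one excised at baseline does. Counted to the end of follow-up, the ratio is unchanged by delay.

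**What zero delayed melanomas would show.** With none delayed among n melanomas, the exact one-sided 95% upper limit is 1 − 0.05^(1/n); for a two-sided 95% interval, replace 0.05 by 0.025.

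| RCM-arm patients × melanoma rate | n | One-sided | Two-sided |
|---|---|---|---|
| 266 × 7.3% | 19 | 14.6% | 17.6% |
| 266 × 14% | 37 | 7.8% | 9.5% |
| 1188 × 7.3% | 87 | 3.4% | 4.2% |
| 1188 × 14% | 166 | 1.8% | 2.2% |

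Excluding 2% with no delayed case needs ln 0.05 / ln 0.98 = 148.3, so 149 melanomas one-sided, or 183 two-sided. Only the last row reaches 149. There, one delayed case raises the one-sided limit to 2.8%. The chance of seeing none is 0.99^166 = 19% if the true rate is 1%, and 0.995^166 = 44% if it is 0.5%.

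**Denominator.** Suppose 12 diagnoses were delayed among 1188 RCM patients. Per patient that is 1.0%, with a one-sided upper limit of 1.6%. Per melanoma it is 12/166 = 7.2% to 12/87 = 13.8%. What the percentage is taken of decides whether the aim is met.

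**The case against.** Several stronger readings are tempting, and the document does not support them.

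- *The ratio rewards missed melanomas.* It does not by itself: missing 10 and sparing nothing moves 13.7 to 15.7. It can improve despite misses, which is a narrower fault.
- *A large loss of melanomas would go unseen.* The statistics section also plans a chi-square comparison of diagnosis frequency between arms. A 32% shortfall at full enrolment, 87 against 59 of 1188 each, gives p = 0.02, so it would probably be noticed. At 266 per arm, 19 against 13 gives p = 0.27. This objection stands in part. But that section does not link the comparison to safety, and the comparison does not measure delay.
- *Under 2% can never be shown.* At the protocol's own 14% with all 2375 contributing, zero delays gives a one-sided limit of 1.8%. The aim is fragile, not impossible.
- *1% contradicts 2%.* An expectation below a target is consistent. The fault is the change from melanoma to cancer and the unclear denominator.
- *The outside benchmark is an error.* The range in "compared with dermoscopy delayed melanoma diagnosis ranging from 7.6 to 16.2" is given as context, and no planned test uses it. Control patients are expected mostly to have immediate biopsy, so the control arm's own delayed rate may be sparse.

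It is also fair to say that decisions and histology are recorded per lesion (*Data collection*), so delayed melanomas can be counted, and that exact intervals may be set out in an analysis plan that is not shown. That does not remove the conflict between definitions, which is in the protocol itself, or the stated aim to prove a bound.

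**Conclusion.** The point holds in a limited form. The statistics section attaches safety to a ratio that other sections of the protocol treat as cost-effectiveness or efficiency. At the targeted 30% saving, that ratio still improves with up to just under 30% of melanomas missed, and it does not register delay. The aim to prove under 2% delayed has almost no support from the planned size. Of the four combinations of arm size and melanoma rate, 2% is excluded in one only, and then only one-sided and with no delayed case.

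This rests on one melanoma per positive patient, complete follow-up, and 7.3% to 14% as the range of melanoma frequency in the RCM arm. The ratio example also assumes that every lesion is excised in the comparison case. The sized comparison of melanomas identified is not affected.

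**What to change.** 1. In *Statistical analysis*, label excisions per melanoma and NNE as efficiency outcomes, in line with the other sections.
2. Define safety as delayed melanomas divided by all melanomas diagnosed to the end of follow-up, where delayed means histologically confirmed in a lesion that was sent to follow-up at the first decision. Report it by arm with exact 95% confidence intervals.
3. Report melanomas per randomised patient by arm beside it, and name this comparison as part of the safety assessment. It covers melanomas that are never found, which the proportion in item 2 cannot.
4. Give the 1% expectation the same condition (melanoma) and the same denominator as the 2% target.
5. In *Expected results*, replace the aim to prove by an aim to estimate, and state the upper limit that the expected melanomas support at both 7.3% and 14%. Keeping a formal claim would mean sizing for it: about 969 RCM-arm melanomas for 80% power to show under 2% (one-sided 95% limit) if the true rate is 1%, or about 386 if it is 0.5%.

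Items 1 to 5, with estimation in place of proof, change wording only and need no extra patients or procedures. The cost is a less favourable safety claim.
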